## Study design

This is a prospective, multicentre, randomized, assessor-masked, 3-arm (1:1:1), active-controlled trial of 360 subjects with meibomian gland dysfunction contributing one study eye. For subjects with both eyes eligible, the eye with the most meibomian gland dropout (meiboscore), fewest expressible meibomian glands, thinnest lipid layer, or lowest TFBUT values (in this order) will be selected as the study eye.

Enrolled patients will be randomized into one of the following groups, 1 month after recruitment during the 15-month study period receiving bilateral treatment of:

Group A: 1-session VTP at month 0

Group B: 4-session IPL+MGX at month 0,1,2,3

Group C: twice daily EW for 15 months

The study will be conducted in accordance with the tenets of the Declaration of Helsinki, and the protocol will be sent for approval by the research ethics review committee of each participating hospital. All participants will provide written informed consent before participation. Study will be registered at ClinicalTrials.gov prior to recruitment. The baseline, follow-up assessments and study procedures will be conducted as described above. Participants will be given contact of the study team to report adverse events at any time, which will also be actively sought at each follow-up visit. Additional follow-up appointment will be provided as and when required.

Recruitment, baseline and follow-up assessment and tear substitutes

Patients will be washed out for 1 month and maintained on one single topical lubricant to be used as frequently as needed from recruitment to study exit (total 16 months). Cool Eye eye drops- hypromellose (3 mg/ml) containing 0.0002 ml of 50% Benzalkonium Chloride solution as preservative will be provided by the research team.

Clinical evaluations are done according to the recommendations of the TFOS DEWS II diagnostic methodology subcommittee at month -1 (recruitment), 0 (baseline), 1, 2, 3, 4, 6, 9, 12, 15 (total 10 visits). Examination is conducted on both eyes starting on the study eye. To minimize the impact on ocular surface and tear film physiology, tests are done from least to most invasive at each follow-up and/or prior to each treatment.

Randomization, masking of assessors

Randomization will be carried out by a computer-generated minimization program. Minimization is a dynamic process to reduce the imbalance between trial arms with respect to a range of predefined prognostic variables, and a randomisation schedule is therefore not drawn up in advance. A form describing the baseline characteristics of each subject according to these minimisation criteria: gender (female, male), age (<45, >45), worst meiboscore (0 vs 1 vs 2 vs 3) from the study eye (lower lid) and referring centres will be filled at recruitment (month-1), returned to Centre for Clinical Research & Biostatistics, CUHK on enrolment. Treatment allocation will be sent to the unmasked trial coordinator for arrangement at baseline (month 0).

IPL or VTP is given by **unmasked treating investigators** not involved in data collection.

**Follow-up investigators** collecting the data are masked to participants’ treatment assignment. This information can be disclosed upon request after the completion of the study.

**Unmasked trial coordinator** will ensure masking by reminding and accompanying each patient before and during visit. Treatment related complications will be evaluated by all participants in a standard datasheet regardless of group assignment. Follow-up investigators will be asked if they know each participant’s group assignment at each visit and why.

Escape rule/withdrawal

Subjects recruited from HA can withdraw their consents at any stage but will be invited to continue follow-up at CUHKEC. They will be managed as per standard of care by referring ophthalmologist. Subject will leave study protocol and be terminated from the study but will be followed and assessed as a study patient if they develop any of the following complications:

1. microbial or marginal keratitis
2. Serious Adverse Event (SAE) potentially attributable to VTP or IPL+MGX

Subjects who develop worsening/progression of their MGD will be managed as per medical standard by their referring ophthalmologist by topical/systemic antibiotics, meibomian gland expression which will be documented as protocol deviation.

## Data processing and analysis

Trial biostatistician will oversee data acquisition, processing and statistical analysis.

Record keeping, confidentiality and monitoring

A unique study number will be assigned to each recruited subject for all study-related documents. The log containing study number to identifiable information will be kept in a locked cabin at the clinical trial office at CUHKEC. All trial-related documents will be maintained by the unmasked trial coordinator to ensure data are accurate, complete, and verifiable from case report forms. Data entry will be cross-checked by a designated technician.

**Primary outcome**: Tear film breakup time (TFBUT) at month 6, month 15

**Secondary outcomes**: Serial measurements of MG, tear-film related parameters, intraocular pressure, compliance to EW, factors associated with MGD outcomes and treatment related complications.

Sample size calculation

Based on Arita et al for IPL+MGX[23] and Lane et al for VTP[24], the estimate mean differences in changes of TFBUT are 3.3 for IPL+MGX and 1.9 for VTP, the pool estimates of SDs are 1.88 for IPL+MGX and 4.04 for VTP. Given a 2.5% type I error (Bonferroni correction) and assuming an average SD of 3, a minimum sample of 88 patients per group can detect a significance difference in change of TFBUT between groups. By assuming a 35% of drop-out over an extended study period (16 months from recruitment), 120 subjects per group are required. This sample size is powered to detect differences between VTP and EW or between IPL and EW given the estimates of EW from Lane et al.

Statistical analysis

The intention-to-treat principle will be applied during the data analysis using Graph Pad Prism version 8.01 (California, USA) and IBM SPSS version 24 (New York, USA) and reported according to CONSORT guidelines for RCT. Categorical data at baseline are analysed using chi-squared or Fisher’s exact tests. Data are presented as mean± SD, or median (IQR) unless otherwise stated. Study outcomes will be compared between groups using pair-wise t-test. Continuity-adjusted chi-squared testing will be applied to compare proportion of patients between treatment arms on secondary outcome. Further comparisons of the primary and secondary outcomes between treatment arms, at baseline and pre-set intervals will be made using risk ratio (RR) for dichotomous data and mean difference for continuous data with 95% confidence interval. Appropriate (logistic or linear) regression models, adjusting for minimisation and outcome variables at baseline will be computed for prognostic factors. Multivariate analyses will be conducted to control with baseline measurements, covariates, and repeated measurements. Correlations between parametric and nonparametric data are assessed with Pearson product-moment correlation or Spearman rank order correlation, respectively. The proportions of eyes developing complications during and after the procedures are compared with Chi-square test. All tests are two-tailed, and p<0.05 is considered significant.

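### The 88 per group does not follow from the stated SD of 3 for either comparison with EW, and 120 enrolled with 35% loss leaves 78, about 75% power for VTP versus EW

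*Protocol*

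**What the plan says.** All the inputs stand in the sample size paragraph of the Protocol, under Data processing and analysis.

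- Effects: "the estimate mean differences in changes of TFBUT are 3.3 for IPL+MGX and 1.9 for VTP".
- Variability: "the pool estimates of SDs are 1.88 for IPL+MGX and 4.04 for VTP".
- Error rate: "Given a 2.5% type I error (Bonferroni correction").
- Result: "assuming an average SD of 3, a minimum sample of 88 patients per group can detect" a difference in change of TFBUT between groups.
- Contrasts covered: "This sample size is powered to detect differences between VTP and EW or between IPL and EW", using EW estimates taken from the cited VTP trial.
- Loss: 35% over the 16 months from recruitment, for which 120 per group are to be enrolled. This agrees with the Study design section: "3-arm (1:1:1), active-controlled trial of 360 subjects".

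The paragraph gives no power, and it does not say which difference was combined with the SD of 3. The statistical analysis paragraph supplies the sidedness: "All tests are two-tailed, and p<0.05 is considered significant".

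**The concern.** A sample size statement should let the reader recover the number from the contrast it is meant to serve. Here the paragraph names two contrasts, both against EW, and one SD. The SD of 3 is close to the simple mean of 1.88 and 4.04 and matches neither source. If that SD does not lead to 88 for the named contrasts, the reader cannot tell which comparison sets the size or what power it has.

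The loss allowance raises a second doubt. If 88 is the minimum number evaluable, 120 enrolled must still yield 88 after the stated loss.

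What is at stake is mainly how a VTP-EW result is read. It has the smaller effect and the larger SD, so it is the comparison with the least margin. A non-significant VTP result means something different at 75% power than at 80% or more.

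**Working it through.** **Inputs.** Differences 1.9 s (VTP) and 3.3 s (IPL+MGX); SDs 1.88, 4.04 and the averaged 3; alpha 0.025 per comparison (0.05/2), two-sided; 1:1 between any two arms; 35% loss; 120 per group enrolled. Power is not stated and is assumed to be 80%. A common SD is assumed in both arms of a comparison, since none is given for EW.

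**Averaged SD.** (1.88 + 4.04)/2 = 2.96, rounded to 3.

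**Formula.** Normal approximation: n per group = 2 × SD² × (z for 0.9875 + z for 0.80)² / difference². The z-values are 2.241 and 0.842; the square of their sum is about 9.505. The t-based n comes from the noncentral t distribution.

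**Reproducing 88.** With SD 3 and the gap 3.3 − 1.9 = 1.4 s: 2 × 9 × 9.505 / 1.96 = 87.3, so 88 (89 by t).

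**The comparisons named, and the alternatives:**

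| Contrast | Difference (s) | SD | n, normal | n, t |
|---|---|---|---|---|
| IPL+MGX vs VTP | 1.4 | 3 | 88 | 89 |
| VTP vs EW | 1.9 | 3 | 48 | 49 |
| IPL+MGX vs EW | 3.3 | 3 | 16 | 18 |
| VTP vs EW | 1.9 | 4.04 | 86 | 88 |
| IPL+MGX vs EW | 3.3 | 1.88 | 7 | 8 |
| IPL+MGX vs EW | 3.3 | 4.04 | 29 | 30 |

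For example, VTP-EW at SD 3 is 171.1 / 3.61 = 47.4, and at SD 4.04 it is 2 × 16.32 × 9.505 / 3.61 = 85.9.

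Two routes therefore lead to 88. One uses the stated SD of 3 but a contrast the paragraph does not name. The other uses a named contrast but not the stated SD.

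**Does the assumed power matter?** At SD 3, VTP-EW needs 64 for 90% power and 77 for 95% (by t). IPL-EW needs 27 for 95%. No conventional power gives 88 for either EW comparison at SD 3. Both routes that do give 88 point to 80%; at 85% they need 98 to 100.

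**Loss.** 88 / (1 − 0.35) = 135.4, so 136. By contrast, 88 × 1.35 = 118.8, so 119, close to the stated 120. That suggests the loss was added as a multiple of 88 rather than taken off the number enrolled. With 120 enrolled, 120 × 0.65 = 78 remain. Keeping 88 of 120 requires a loss of at most 1 − 88/120 = 26.7%.

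**Power for VTP-EW, 1.9 s, SD 4.04 (t, with normal in brackets):**

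- 88 per group: 80.4% (81.0%)
- 78 per group: 74.9% (75.7%)
- 120 per group, no loss: 91.7% (92.0%)

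IPL-EW is above 99% at 78 with SD 1.88, 3 or 4.04.

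**The case against.** The strongest reply is that 88 is not wrong. It follows from the stated SD of 3 and the 1.4 s gap, and the text first speaks only of a difference between groups. One could read it as sizing for the smallest gap and then noting that the larger differences from EW are covered. IPL+MGX versus VTP is not irrelevant either, because hypotheses 2 and 3 concern which treatment acts earlier or lasts longer. And VTP-EW at its own SD of 4.04 also needs 86 to 88.

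Most of this stands. A reader might infer that 88 is a calculation error, and the documents do not support that. What remains is that the primary objective and hypothesis 1 compare each treatment with EW, the paragraph claims power for those contrasts only, and its stated SD does not lead to 88 for them.

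A second tempting inference is that the protocol overstates VTP-EW power by 17 to 20 percentage points, because SD 3 would imply 97.3% at 88 and 95.4% at 78. The protocol states no power at all, so no such figure can be attributed to it.

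A third is that the averaged SD causes the fall from 80% to 75%. It does not: that fall comes entirely from 78 rather than 88 evaluable patients, that is, from the loss allowance.

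Finally, choosing a common planning SD is legitimate in itself, and both SDs come from outside studies. The SD of 4.04 is used here because the protocol assigns it to VTP, not because it is known to hold in this population. The 35% loss is stated for the full 16 months, so month 6 may have more than 78 evaluable.

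**Conclusion.** The point holds as a mismatch between the stated basis and the stated claim, together with a loss allowance that does not deliver the stated minimum. At SD 3 the EW comparisons need 49 and 18, not 88. The 88 suits VTP-EW only at SD 4.04, where it gives 80.4% power. After the protocol's own 35% loss, 78 per group remain and VTP-EW has 74.9%, about 5.5 percentage points less. IPL-EW is unaffected, above 99%.

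The VTP-EW figures rest on 1.9 s and SD 4.04 applying to both arms, two-sided alpha 0.025, and the full 35% loss having occurred. They describe month 15; power at month 6 lies between about 75% and 92%, depending on loss by then.

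This is a defect in the written justification. It does not show that the trial is too small to proceed or that enrolment has to change.

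**What to change.** Rewrite the sample size paragraph:

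- Remove the averaged SD.
- Give each EW comparison its own line with difference, SD, two-sided alpha 0.025 and power: VTP-EW 1.9 s with SD 4.04, and IPL-EW 3.3 s with the SD chosen for it.
- Name VTP-EW as the comparison that sets the size: 88 evaluable per group for 80% power.
- State that 120 per group with 35% loss gives 78 evaluable, with about 75% power for VTP-EW and over 99% for IPL-EW. Alternatively, state that 120 keeps 88 evaluable only if loss is at most about 27%, and justify that lower loss.
- If the 1.4 s contrast between IPL+MGX and VTP was in fact the basis, say so and say what role that comparison has.

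The cost is a reworded paragraph and a less comfortable figure for VTP-EW. Enrolment stays at 360.

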# Plan of investigation

## Subjects

A total of 360 patients with symptomatic MGD will be recruited from the participating hospitals coordinated by the Chinese University of Hong Kong (CUHK) Research Clinic, the CUHK Eye Centre (CUHKEC), Department of Ophthalmology and Visual Science, Faculty of Medicine, The CUHK. Open recruitment will be made possible by the use of online channels, as well as promotional flyers and QR codes to be distributed at the participating hospitals. We adopt some of the inclusion and exclusion criteria of recent RCT on MGD [18-19].

Inclusion criteria include:

1. ≥18 years of age with no upper age limit;
2. Providing informed consent, agree to attend follow-up visits and comply to treatment regimen
3. Symptomatic dry eye TFBUT ≤ 5 seconds and OSDI ≥ 13[20];
4. Mild to moderate (level 3-4) MGD on at least one eye[21];
5. Fitzpatrick skin type 1-4.

Exclusion criteria are:

1. Contact lens wear 3 months before or during the study period;
2. Use of topical (including anti-glaucomatous, cyclosporin, antibiotics) or systemic medication known to affect (worsen or improve) MGD 3 months before or during the study period;
3. Major systemic (e.g. Sjogren’s syndrome), dermatologic (e.g. Rosacea) known to affect MGD or ocular conditions (including thyroid eye disease, recurrent conjunctivitis, ocular allergies);
4. Ocular procedures (excluding uncomplicated cataract operation) 3 months before and any ocular procedure during the study period;
5. History of vision correction surgery or plan to undergo the procedure during the study period;
6. Dermatological treatment (including chemical peeling, laser, IPL or energy device in the periocular and facial region) 6 months before or during the study period;
7. Contraindications to IPL therapy (including recent sun-burn, photosensitivity, active or pigmented skin lesions, cancer, implants, tattoos, semi-permanent makeup in the periocular area);
8. Contraindications to VTP therapy (ocular surgery, ocular injury, ocular herpes of eye or eyelid, and ocular inflammation 3 months before the study; active ocular infection, etc.);
9. Women who are pregnant, nursing, planning pregnancy, or of childbearing potential not using a reliable method of contraception.

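### 120 per group with the assumed 35% drop-out leaves 78 at month 15, ten below the protocol's own minimum of 88

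*Protocol*

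**What the plan says.** The sample size paragraph (Protocol, Data processing and analysis) first sets the base figure: "a minimum sample of 88 patients per group can detect a significance difference in change of TFBUT between groups". It then makes the allowance for loss: "By assuming a 35% of drop-out over an extended study period (16 months from recruitment), 120 subjects per group are required". The enrolment target follows from this. The Subjects section says "A total of 360 patients with symptomatic MGD will be recruited", and the Study design section describes a "3-arm (1:1:1), active-controlled trial of 360 subjects", which is 120 per arm.

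The planning inputs are in the same paragraph: "the estimate mean differences in changes of TFBUT are 3.3 for IPL+MGX and 1.9 for VTP"; source SDs of 1.88 (IPL+MGX) and 4.04 (VTP); a type I error of 2.5% after Bonferroni correction; and a calculation "assuming an average SD of 3". The comparisons named as powered are VTP with warm compress (EW) and IPL with EW. No power is stated, and the paragraph does not say which difference produced 88. The primary outcome is TFBUT at month 6 and at month 15.

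**The concern.** A minimum number of patients per group, an assumed loss and an enrolment figure have to agree: enrolment times the retained fraction must be at least the minimum. Here it is not. No other part of the Protocol gives a different drop-out rate or explains the step from 88 to 120.

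The sample size justification will be carried into the trial report, since the Statistical analysis section commits to CONSORT reporting. As written, it presents 120 per group as sufficient for a minimum that the plan, on its own loss assumption, does not expect to reach at month 15.

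**Working it through.** **Inputs.** Minimum 88 per group, loss 35% over 16 months from recruitment, enrolment 120 per group, differences 3.3 s and 1.9 s, working SD 3, source SD for VTP 4.04 and alpha 2.5% all come from the sample size paragraph. Two-sidedness comes from the Statistical analysis section ("All tests are two-tailed, and p<0.05 is considered significant"). I use the planning level of 2.5% throughout; the 0.05 in that sentence is a separate matter.

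**1. Where 120 probably comes from.** 88 × 1.35 = 118.8, which rounds up to 119 and then to 120 as a round number. The Protocol does not show this step, so it is an inference. Nothing below depends on it.

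**2. What the stated loss implies.**
- Remaining at 35% loss: 120 × (1 − 0.35) = 78 per group.
- Shortfall: 88 − 78 = 10 per group, or 10/88 = 11%.
- Enrolment that keeps 88: 88/(1 − 0.35) = 135.4, so 136 per group, 408 in total. That is 16 per group and 48 overall more than planned.
- Largest loss at which 120 keeps 88: 1 − 88/120 = 26.7%. In whole percentages, 26% leaves 88.8 and 27% leaves 87.6.

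**3. What 88 might rest on.** The normal approximation is n = 2(SD/difference)²(z₁ + z₂)², with z₁ = 2.241 (two-sided 0.025), z₂ = 0.842 (80% power, assumed) and (z₁ + z₂)² = 9.505.
- 1.4 s (3.3 − 1.9) with SD 3: 2 × (3/1.4)² × 9.505 = 87.3, so 88.
- 1.9 s with SD 4.04: 2 × (4.04/1.9)² × 9.505 = 86.0 (85.95), so 86; the t-test version gives 87.2, so 88.
- 1.9 s with SD 3: 2 × (3/1.9)² × 9.505 = 47.4, so 48, which is far from 88.

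Two readings therefore reproduce 88 at about 80% power. Both are back-solved. The first uses a difference between IPL+MGX and VTP that the paragraph does not name as a powered comparison; the second uses an SD other than the one it says it assumed.

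**4. Power at 88 and at 78** (noncentral t, two-sided alpha 0.025; 1.9 s and 3.3 s are read as differences from EW, as the last sentence of the paragraph suggests):

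| Difference | SD | 88 per group | 78 per group |
|---|---|---|---|
| 1.4 s | 3 | 79.7% | 74.2% |
| 1.9 s | 4.04 | 80.4% | 74.9% |
| 1.9 s (VTP with EW) | 3 | 97.3% | 95.4% |
| 3.3 s (IPL+MGX with EW) | 3 | about 100% | about 100% |

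For any fixed power and SD, the detectable difference grows by about √(88/78) = 1.06, that is by 6%.

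**5. Month 6.** The 35% is stated for the full 16 months. Month 6 is 7 months after recruitment. If loss is spread evenly (an assumption), it is 35% × 7/16 = 15.3% by then, leaving about 102 per group; at a constant rate of loss, 120 × 0.65^(7/16) leaves about 99. Both exceed 88, so the shortfall concerns month 15.

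**The case against.** The strongest reply is that the trial may still be amply powered for what it says it is powered for. On the stated SD of 3 and the stated differences, 78 completers give 95.4% power for VTP with EW and practically full power for IPL+MGX with EW. This stands. A reader might infer from the shortfall that 360 patients are too few, or that the month-15 comparison is underpowered. The Protocol does not support that: it sets no power target, does not say which difference produced 88, and on its named comparisons and working SD the loss of 10 per group costs about 2 percentage points at most. The reply is not complete, however. The paragraph also reports an SD of 4.04 for VTP, and at that value the VTP comparison has 74.9% power.

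A second reply is that analysis by intention to treat keeps everyone in. It does not remove the mismatch. The paragraph inflates 88 for drop-out, so it treats drop-outs as lost to the comparison. The Statistical analysis section also mentions regression adjusted for baseline and analyses of repeated measurements, but the sample size calculation takes no credit for them.

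A third reply is that month 6 is also primary and probably unaffected. That is correct and limits the point to month 15. Rounding explains nothing: going from 119 to 120 adds one patient, while the enrolment gap is 16 per group.

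**Conclusion.** The point holds as an arithmetic inconsistency. A minimum of 88, a loss of 35% and an enrolment of 120 cannot all stand: the stated loss leaves 78 per group at month 15, 10 short, and 136 would be needed to keep 88. This uses only the Protocol's own figures and does not depend on how 120 was reached.

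The effect on power is conditional. If 88 was built on 1.4 s with SD 3, or on 1.9 s with SD 4.04, power falls by about 5.5 points to 74% or 75%. If the named comparisons with EW and the SD of 3 are what matter, it stays at 95% or more. The multiplication by 1.35 is the likely cause but is not documented, so it should not be reported as fact. The importance is moderate: the justification is wrong as written and should be corrected, but inadequate power is not shown.

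**What to change.** Keep 120 per group and rewrite the end of the sample size paragraph to say that:
- with 35% loss over 16 months, 120 enrolled leaves 78 evaluable per group at month 15;
- 88 evaluable per group is kept only if loss is no more than about 26%;
- the figure of 88 rests on a stated difference, SD and power, which the sponsor supplies from its own calculation;
- the power at 78 on those same inputs is the figure given for month 15.

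Delete the statement that 120 are required. The power at 78 should come from the sponsor's actual inputs. The 74% to 75% above should not be copied in, because it rests on back-solved values.

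The cost is a few sentences and, depending on the inputs, a somewhat less favourable power for month 15. Enrolment does not change. If the sponsor instead wants 88 guaranteed at 35% loss, the price is 136 per group, 408 in total, which is 48 more patients.

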# Aims and hypotheses to be tested

Primary Objective

To compare the efficacy and safety of 1-session vectored thermal pulsation (VTP) or 4-session intense pulsed light and meibomian gland expression (IPL+MGX) with twice-daily eyelid warm compress (EW) therapy for meibomian gland dysfunction (MGD)

Secondary Objectives

1. To compare the course of MGD among groups over 15 months (12-month after final IPL+MGX)
2. To identify factors predicting responses and compliance to therapies

Hypotheses

1. Both 1-session VTP and 4-session IPL+MGX are more efficacious than twice-daily EW in improving MGD
2. MGD improves earlier after VTP
3. MGD improvement lasts longer after 4-session IPL+MGX

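### Complications fall under two conflicting chi-square rules, one per patient and one per eye, and the only stated effect measure, the risk ratio, is undefined if the EW arm has no events

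*Protocol*

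**What the plan says.** The primary objective (Protocol, Aims and hypotheses to be tested) is "To compare the efficacy and safety of 1-session vectored thermal pulsation (VTP) or 4-session intense pulsed light and meibomian gland expression (IPL+MGX") against twice-daily EW. Under Data processing and analysis the primary outcome is "Tear film breakup time (TFBUT) at month 6, month 15", and the list of secondary outcomes ends with "compliance to EW, factors associated with MGD outcomes and treatment related complications".

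The Statistical analysis section then has four statements that bear on complications:

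- For secondary outcomes in general: "Continuity-adjusted chi-squared testing will be applied to compare proportion of patients between treatment arms on secondary outcome". The unit is the patient and the test is continuity-adjusted.
- For complications in particular, a sentence near the end of the paragraph compares the proportions of eyes affected by a chi-square test. The unit is the eye and no continuity adjustment is named.
- For effect size, comparisons "will be made using risk ratio (RR) for dichotomous data and mean difference for continuous data with 95% confidence interval".
- For the decision level: "All tests are two-tailed, and p<0.05 is considered significant".

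The Study design section says that treatment is bilateral, that each subject contributes one study eye, and that both eyes are examined. The safety block of the Study Table mixes items that belong to an eye (iris defect, lens opacity) with items that belong to a patient (facial redness, swelling, bruises, pigmentation). No tolerable excess risk and no risk difference is stated.

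**The concern.** Complications are a secondary outcome, so both test sentences apply to them, and they differ in both test and unit. With few events the continuity adjustment matters a good deal, so the same data can be called significant or not according to the sentence followed. Counting both eyes of bilaterally treated patients in an ordinary chi-square also treats correlated observations as independent.

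The effect measure adds a second difficulty. Some of the listed harms, such as iris defect or loss of lashes, are plausible after a light or thermal device and implausible after a warm towel. The EW arm may well have no such events, and the risk ratio then has a zero denominator. The interval meant to express the size of the excess is lost in the case where it is most needed, leaving a p-value that depends on an unresolved choice of test. What is at stake is the safety half of the primary objective.

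**Working it through.** **Inputs.** The protocol gives no sizing figure for safety. The sample size calculation, based on TFBUT, gives 88 per group, raised to 120 for 35% drop-out. The 88 is reproduced by a two-sided 2.5% level, SD 3, a difference of 3.3 − 1.9 = 1.4 and 80% power; the difference and the power are inferred, not stated. 88 × 1.35 = 119, close to the stated 120. If 35% of 120 are lost, 120 × 0.65 = 78 remain. Complication rates are not given, so those used below are assumptions.

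**Step 1: the two tests.** For x events of n against 0 of n, compared pairwise, the statistics reduce to

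- plain: 2n·x / (2n − x)
- continuity-adjusted: 2n·(x − 1)² / [x(2n − x)]

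Each is compared with 3.841 (1 df, two-sided 0.05). With n = 120:

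| Events | Plain | p | Adjusted | p |
|---|---|---|---|---|
| 3 vs 0 | 720/237 = 3.04 | 0.081 | 960/711 = 1.35 | 0.245 |
| 4 vs 0 | 960/236 = 4.07 | 0.044 | 2160/944 = 2.29 | 0.130 |
| 5 vs 0 | 1200/235 = 5.11 | 0.024 | 3840/1175 = 3.27 | 0.071 |
| 6 vs 0 | 1440/234 = 6.15 | 0.013 | 6000/1404 = 4.27 | 0.039 |

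The largest split that stays non-significant is 3 vs 0 (plain) or 5 vs 0 (adjusted). These limits are the same at n = 78, at n = 88 and at 240 eyes per arm.

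**Step 2: the unit.** Suppose five patients are injured in both eyes and none in EW. Counted by patient, p is 0.024 (plain) or 0.071 (adjusted). Counted as 10 of 240 eyes against 0 of 240, the plain statistic is 480 × 10 / 470 = 10.2, p about 0.001. Nothing has been added except a second eye from each of the same five patients.

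**Step 3: ratio against difference, 5/120 vs 0/120.**

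- Risk ratio: (5/120)/(0/120), undefined. Adding 0.5 to each cell gives 5.5/0.5 = 11.0. The standard error of its logarithm is √(1/5.5 − 1/120.5 + 1/0.5 − 1/120.5) = 1.47, so the 95% CI is 0.61 to 197, which is uninformative.
- Risk difference: 5/120 − 0 = 4.2%. The Wilson limits are 1.8% to 9.4% for 5/120 and 0% to 3.1% for 0/120. Newcombe's lower limit is 4.17 − √((4.17 − 1.79)² + 3.10²) = 0.3%, and the upper limit is 9.4%.

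**Step 4: how often an excess is missed (p ≥ 0.05), n = 120 per arm, assumed rates.**

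| True rates | Adjusted | Plain |
|---|---|---|
| 3% vs 0% | 85% | 51% |
| 5% vs 0% | 44% | 14% |
| 5% vs 1% | 72% | 56% |
| 10% vs 2% | 33% | 21% |

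The first row follows from step 1: with 3% of 120, the chance of at least 6 events is 0.153 and of at least 4 is 0.487. At n = 78 the first row becomes 97% and 79%.

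**Step 5: what zero events would show.** With 0 of n events, the exact one-sided 95% upper bound on incidence is 1 − 0.05^(1/n): 2.5% at n = 120 and 3.8% at n = 78.

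**The case against.** The case on the other side is substantial.

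- A reader might infer that 5 injured patients of 120 against none would simply be reported as not significant. That holds only under the general sentence. The sentence written for complications names a plain chi-square, under which 5 vs 0 gives p = 0.024.
- A reader might say that the plan puts no bound on excess harm. It does attach a 95% interval to the risk ratio. The fault is that this interval cannot be formed in the ordinary way when EW has no events.
- A reader might conclude that harm is missed most of the time. In two of the four assumed scenarios at 120 per arm it is detected more often than not under either test. The 78 per arm is also pessimistic for early procedural events, since the 35% loss accrues over 16 months and the procedures fall in months 0 to 3.
- The protocol nowhere says that non-significance will be read as equal safety. Its hypotheses concern efficacy only, and sizing a trial on its efficacy outcome is ordinary practice.
- The choice of interval and the handling of zero cells are often left to a statistical analysis plan, which is not at hand.
- The eye-based sentence may mean study eyes only, in which case there is one eye per patient and no clustering.

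All of this limits the point, but two things stand. The conflict of test and unit is in the protocol's own text, as is the choice of the ratio scale. The eye-based sentence does not say whether it means study eyes or all treated eyes, and facial complications cannot be counted by eye at all.

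**Conclusion.** The point holds in limited form. The protocol states two incompatible analyses of complications. For 4 or 5 events against none in 120 per arm, significance flips between them. If both treated eyes are counted, the eye-based version also overstates the information. The risk ratio fails when the EW arm has no events, whichever test is used, while the risk difference remains interpretable.

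The figures assume pairwise comparisons at two-sided 0.05 and, in step 4, complication rates that the document does not supply. That EW will have no events is realistic for device-specific injuries but is an assumption; it is less obvious for redness or swelling. The document does not support the wider reading that the plan would declare the devices safe on a non-significant test. That is a foreseeable misuse which the wording leaves open. The efficacy analysis is not touched.

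**What to change.** 1. Replace the two sentences by one per-patient analysis of complications. A patient counts once if either eye or the facial skin is affected. Results by eye, if wanted, should be descriptive or allow for the pairing of eyes.
2. For complications, report the risk difference (VTP minus EW, IPL+MGX minus EW) with a Newcombe or Miettinen-Nurminen 95% CI in place of the risk ratio.
3. Add an exact (Clopper-Pearson) upper bound on incidence in each arm, overall and for iris, lens, lash or eyebrow, and skin events. State whether the bound is one- or two-sided.
4. State that the conclusion on safety rests on these intervals and that p > 0.05 is not evidence of equal safety.

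The cost is some wording and a few lines of analysis, with no new data. The safety statement will look less favourable: even with no events in 120 patients the one-sided bound is 2.5%, and after a few events the upper limits reach several percent.
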